### Mechanistic analysis

Analysis of the biomarkers from stored blood will be performed using the same linear mixed model as for the analysis of K-BILD. Analysis of routine microbiology and 16S ribosomal ribonucleic acid (rRNA) sequence data will be descriptive by tabulating the different types of microbiological cultures and their relative prevalence or signal strength.

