As the pathogenesis of IPF is unknown the potential mechanisms of action of co-trimoxazole are uncertain. Co-trimoxazole is a broad-spectrum antibiotic with bactericidal effects against respiratory pathogens and the role of infection in IPF is becoming more evident [14]. However, it may have non-antimicrobial effects, targeting cellular processes that have been implicated in the pathogenesis of IPF. An evaluation of efficacy by a clinical trial that is adequately powered to detect clinically important differences on clinically relevant endpoints is required before this treatment can be considered in clinical practice.

The Efficacy and Mechanism Evaluation of Treating Idiopathic Pulmonary fibrosis with the Addition of Co-trimoxazole (EME-TIPAC) trial is designed to test the hypothesis that treating IPF patients with co-trimoxazole will increase the time to death (all causes), lung transplant or first non-elective hospital admission compared to standard care, as defined by the National Institute for Health and Care Excellence (NICE) guidelines [15], in patients with moderate to severe disease (FVC ≤ 75% predicted). Secondary objectives are to compare the clinical efficacy of this intervention in terms of respiratory-related hospital admission, death, health-related quality of life, QALYs, cough score and quality of life, lung function and oxygen saturations. Secondary mechanistic aims are to investigate the effect on (1) the lung microbiota and other measures of infection, (2) markers of epithelial injury and (3) markers of neutrophil activity. An exploratory aim is to determine whether the mechanistic properties are related to clinical efficacy.

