### Peripheral blood

Peripheral blood is being taken at baseline, 3, 6 and 12 months and at the end of the trial and stored for analysis of measures of (1) infection/inflammation, including C-reactive protein (CRP), which is an acute-phase serum protein that is increased in concentration in patients with inflammation and is a significant prognostic indicator for survival in patients with IPF [26]; (2) alveolar epithelial injury including surfactant protein (SP)-D which is elevated in serum in patients with IPF [27] and predicts mortality [28] and matrix metalloproteinase (MMP)-7 which is related to disease severity [29, 30] and is an independent predictor of mortality [31] and (3) neutrophil activity, including myeloperoxidase, which is almost exclusively expressed in neutrophils and is a marker of their activation and degranulation.

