### Routine microbiology

Sputum is being obtained, where possible, and sent for local microbiological culture and susceptibility testing; and a nasal swab will be sent for viral culture, if clinically indicated, in all patients.

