Co-trimoxazole may be exerting its effect by either antibiotic or non-antibiotic mechanisms. Infection is common in patients with IPF – even amongst those not receiving immunosuppression. In a meta-analysis of patients allocated to placebo from clinical trials of patients with IPF, reported rates of pneumonia were 37.1 per 1000 patient years in studies not permitting immunosuppression [39] which is even higher than in chronic obstructive pulmonary disease [42]. More than one third of patients with IPF are colonised with pathogenic bacteria [43] or *Pneumocystis jirovecii* [44], most of which are susceptible to co-trimoxazole. Two independent groups of researchers using 16S technology have shown that a heavy bacterial load [15] and a lung microbiota profile enriched with *Streptococcus* and *Staphylococcus* spp. [45] predict poor outcomes in IPF. We have chosen to monitor an antibiotic effect by capturing routine microbiological data for all patients.

Alternatively or additionally, co-trimoxazole may also have non-antimicrobial effects, particularly on neutrophil function. Sulphamethoxazole-related sulphonamides have effects on neutrophil chemotaxis [46] and superoxide production [47]. Co-trimoxazole or its individual components (trimethoprim and sulfamethoxazole) also inhibit neutrophil post-phagocytic, myeloperoxidase-mediated protein iodination [48] and neutrophil respiratory burst [49, 50]. Oxidant stress has been implicated in alveolar epithelial injury [51], and epithelial-mesenchymal transition [52] in IPF, and IPF patients have increased concentrations of 8-isoprostane in exhaled breath condensate [53]. Moreover, neutrophils have an important role in causing oxidant stress in IPF [54], and neutrophilic alveolitis features frequently [55]. Furthermore, higher neutrophil counts in sputum are associated with worse lung function [56] and the percentage of bronchoalveolar lavage fluid (BALF) neutrophils at diagnosis is an independent predictor of mortality [57]. We will be assessing disease-modifying effects of co-trimoxazole by assessing recognised prognostic biomarkers in the serum in all patients who will also undergo measurement of neutrophil elastase at the end of the trial.

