It is inevitable that many participants enrolled in this trial will be frail in view of their age and disease severity. For this reason we decided to keep the research burden to a minimum. The project has been designed so that the trial visits align with routine follow-up assessments for IPF patients, and the visit time points are sufficiently flexible to permit this. In addition (1) we have, for two of the visits, permitted safety blood tests to be undertaken in primary care and (2) have allowed adverse event assessments to be undertaken by phone.

This trial will determine whether co-trimoxazole is efficacious in terms of reducing mortality and or hospitalisation and should also provide some insight into its mechanism of action. Should it be found to have beneficial effects due to its antibiotic activity, further studies may be undertaken using narrower-spectrum antibiotics. Alternatively, if its activity is due to non-antibiotic mechanisms, such as effects on neutrophil activity in IPF, further lines of research may be possible using drugs targeting these mechanisms but lacking antimicrobial activity, thereby obviating the collateral risks of disrupting gut flora and selecting resistance.

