### Protocol amendments

We modified the protocol in February 2015 as we became aware of new data regarding the risks of hyperkalaemia with co-trimoxazole [19]. We started to exclude participants with a serum potassium greater than 5.0 mmol/L and increase monitoring of participants with a baseline serum potassium of between 4.7 and 5.0 mmol/L who are 66 years old or over and taking potassium-sparing diuretics.

We modified the protocol in May 2016 to widen recruitment criteria to make the trial more generalisable, taking in to account feedback from sites, the TMG and TSC. We removed a requirement for participants to be diagnosed within 2 years of entry into the trial. This exclusion criterion was originally included to prevent stable patients entering into the trial; however, the time of diagnosis was sometimes difficult to determine and also patients with stable disease are unlikely to have significantly reduced lung function (FVC). We increased the maximum FVC value from 70% predicted to 75% predicted as this permitted increased recruitment without reducing the anticipated event rate. We also permitted the 6-week and 9-month visits to be undertaken via the phone with local assessment of safety bloods in order to reduce the patient burden and increase acceptability.

The protocol also included a bronchoscopy sub-study at a small number of selected sites, at which bronchoalveolar lavage fluid would be obtained from a sub-set of 50 participants at baseline and then at 3 months post commencement of trial treatment. However, following recommendations by the DMC and TSC, recruitment to the sub-study was suspended due to a lack of recruitment. As a result it has not been included in this paper.

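### A lung-microbiota aim and a 16S analysis remain after the lavage sub-study was suspended; no specimen is tied to 16S, microbiology is only tabulated, and elastase sampling is unclear

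*Protocol article*

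**What the plan says.** **Aim.** The Background section lists the secondary mechanistic aims: "Secondary mechanistic aims are to investigate the effect on (1) the lung microbiota and other measures of infection", followed by markers of epithelial injury and of neutrophil activity. The Discussion part of the Abstract repeats the microbiota aim. The link from mechanism to clinical efficacy is labelled exploratory.

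**Analysis.** The Mechanistic analysis section says: "Analysis of routine microbiology and 16S ribosomal ribonucleic acid (rRNA) sequence data will be descriptive by tabulating the different types of microbiological cultures". The tables are also to show how common each type is, or how strong its signal. Biomarkers from stored blood are instead analysed with the mixed model used for K-BILD.

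**Specimens.** The Protocol amendments section describes a lavage sub-study of 50 participants at baseline and 3 months, then reports that "recruitment to the sub-study was suspended due to a lack of recruitment" and that the paper leaves it out. The Routine microbiology section says: "Sputum is being obtained, where possible, and sent for local microbiological culture and susceptibility testing". A nasal swab is sent for viral culture only when there is a clinical reason.

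**Blood and elastase.** The Peripheral blood section says: "Peripheral blood is being taken at baseline, 3, 6 and 12 months and at the end of the trial and stored". It names CRP, SP-D, MMP-7 and myeloperoxidase. The Biomarkers section names an elastase assay but neither a specimen nor sampling times. The main Discussion says of all patients "who will also undergo measurement of neutrophil elastase at the end of the trial".

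**The concern.** The article states an aim and an analysis, reports that recruitment to the lavage sub-study was suspended, and leaves the aim and analysis as they were. Nothing that remains is assigned to sequencing.

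The aim is also an effect of treatment, whereas the stated analysis is a table. A table of culture types gives no effect size and no interval. Sputum is obtained only from patients who can produce it, and production is observed after randomisation. If co-trimoxazole changes sputum production, prevalence among producers compares differently selected groups.

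The elastase wording can be read as one sample at trial end. By then many patients would have had a primary event, which under Methods/design is also when trial medication stops, and the arms would differ in how many.

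The results are meant to guide later work. The Discussion section considers one research direction "Should it be found to have beneficial effects due to its antibiotic activity" and another if the activity is non-antibiotic. The antibiotic side of that contrast is where the plan is thinnest.

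**Working it through.** The document gives no sample size, power or error rate for the mechanistic analyses, so there is no stated figure to reproduce. The first and second steps set sections side by side; the third is arithmetic.

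**1. Which specimen could supply each mechanistic measure?**

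| Measure | Specimen stated | Timing stated | Stated analysis |
|---|---|---|---|
| 16S / lung microbiota | none; lavage recruitment suspended | none | tabulation |
| Routine culture | sputum where obtainable | visit schedule in Secondary outcomes (baseline, 3 and 6 months, then 6-monthly, plus end of trial or hospitalisation) | tabulation |
| CRP, SP-D, MMP-7, myeloperoxidase | stored blood | baseline, 3, 6, 12 months, trial end | K-BILD mixed model, comparing arms |
| Elastase | none | trial end (main Discussion) | not stated separately |

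The 16S row has an analysis but no specimen. The main Discussion itself relies on routine microbiology, not sequencing, to monitor an antibiotic effect.

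**2. What does the elastase wording allow?** It may mean sampling at trial end, or a batch assay at trial end of blood stored throughout. The Biomarkers section says SP-D and MMP-7 are measured as they are in peripheral blood, which suggests that the paragraph was written with another specimen in mind. The document does not settle it.

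**3. How much would the timing matter if elastase were sampled only at trial end?**

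Inputs from the Sample size section: medians of 28.8 months (control) and 51.1 months (active), 30 months of recruitment and 12 further months of follow-up. Assumptions: exponential event times, and potential follow-up uniform on 12 to 42 months.

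With λ = ln 2 / median, the probability of a primary event by trial close is

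P = 1 − [exp(−12λ) − exp(−42λ)] / (30λ).

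- Control: λ = 0.02407; P = 1 − (0.749 − 0.364)/0.722 = 0.466.
- Active: λ = 0.01356; P = 1 − (0.850 − 0.566)/0.407 = 0.302.
- Mean of the two arms: 0.384. The plan's own 96 events in 264 patients is 96/264 = 36%, the same scale.

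Event-free at 3 months:

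- Control: 0.5^(3/28.8) = 0.930.
- Active: 0.5^(3/51.1) = 0.960.

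The arms differ by about 16 percentage points in events by trial close and by 3 points at 3 months. An early stored sample is therefore much less exposed to selection by events and stopped treatment.

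**The case against.** The strongest reply is that this is a condensed article. The full protocol may name a 16S specimen, and full analysis details are deferred to an analysis plan that is not shown. Describing microbiology without a model is a declared choice, reasonable when cultures are sparse, and a table can show the arms side by side. This part stands: the matter concerns secondary mechanistic aims and does not touch the primary analysis. It does not remove the inconsistency, because the article itself states the aim, the analysis and the suspension, and does not reconcile them. Nor does a table by arm supply an effect estimate.

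Three stronger readings are tempting, and the document does not support them.

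- **The antibiotic-versus-neutrophil question cannot be answered.** CRP is a serial measure of infection and inflammation, and myeloperoxidase a serial neutrophil marker. Both fall under a model that compares arms. The aim also covers "the lung microbiota and other measures of infection", so culture data still serve part of it. The Discussion section promises only some insight into mechanism.
- **No lavage exists.** Recruitment was suspended. The text does not say that nothing was collected, or that samples were discarded.
- **Elastase will be compared with only about 60% of patients on drug.** This rests on one reading of the timing. Patients who have died give no closing sample. Because the closing measurement point is shared with hospitalisation, a patient whose event is an admission may be sampled at that admission, not at trial close. The 47% and 30% are proportions with a primary event, not proportions sampled off drug.

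It might also seem natural to score patients without sputum as having no pathogen and to make that the single main analysis. That treats a missing specimen as a negative result, so an effect on sputum production would look like an antibacterial effect. Leaving out samples taken during an admission would likewise condition on a component of the primary outcome.

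**Conclusion.** The point holds, limited to three parts.

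- **16S and lung microbiota.** The aim and the analysis have no stated specimen once recruitment to the 50-participant lavage sub-study is suspended. The article is inconsistent here, whatever the full protocol says.
- **Microbiology analysis.** A tabulation is fixed for an aim about a treatment effect, with no between-arm estimate or interval.
- **Elastase.** Specimen and sampling times are unclear. If sampling is at trial end only, about 47% of control and 30% of active patients would have had a primary event by then, against about 7% and 4% at 3 months (1 − 0.930 and 1 − 0.960). These figures assume exponential events at the planned medians and uniform follow-up of 12 to 42 months.

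The serial blood markers are unaffected. The mechanistic programme is weakened on its microbiota part and is not unanswerable. The change is worth making before database lock because it is cheap and improves what the trial can say about mechanism.

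**What to change.** 1. **Reconcile the Abstract, Background, Mechanistic analysis and Protocol amendments sections.** Tie 16S to a sample the trial actually holds. Otherwise withdraw the 16S analysis and restate the aim as the effect on routine sputum culture and other measures of infection.
2. **In Mechanistic analysis, keep the table and add a between-arm comparison.** At 3, 6 and 12 months, compare the proportion of attending randomised patients with a pathogen isolated. Give a 95% confidence interval and adjust for licensed IPF medication and site, as the Statistical analysis section does elsewhere. Report sputum production by arm, and show results both for all attenders and for producers only, because production is itself post-randomisation.
3. **Reconcile the elastase wording in the Biomarkers section and the main Discussion.** State specimen and sampling times. If it is a blood assay, analyse it on the serial stored samples, at least baseline and 3 months, with the model already planned for stored-blood biomarkers, and not only at trial end.

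Cost: wording and one added model. If the assay budget is fixed, some elastase assays may have to move from the end-of-trial sample to earlier ones. Sparse cultures will give wide intervals, and a restated aim is narrower than the present one.

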### Dissemination

The results of the trial will be published regardless of the direction of effect.

All patients participating in the trial will, at the end of the trial, be provided with a letter detailing their treatment allocation with a lay summary of the trial outcomes. General practitioners of patients participating in the trial will also be given a copy of the trial results.

## Discussion

IPF is a progressive and usually fatal lung disease with a 5-year survival of 20–40% [36]. The aetiology for the majority of patients is unclear and there are limited treatment options. The EME-TIPAC trial should determine whether the addition of co-trimoxazole to current standard care improves patient-relevant outcomes in moderate and severe disease and should explore how co-trimoxazole may be working.

There is much debate about the choice of primary endpoint for clinical trials of IPF. Our primary outcome of time to death (all causes), transplant or first non-elective hospital admission is clinically important. These endpoints have been recommended by the Pulmonary Fibrosis Foundation for phase 3 clinical trials in IPF [37]. Many trials use surrogate markers of disease progression, most commonly lung function measures such as FVC. These have the advantage that they are inexpensive and relatively easy to determine, but are not reliable, validated or adequately robust [37]. Some researchers have claimed that the change in FVC should be used as an endpoint, claiming that a mortality endpoint requires unfeasibly large studies in mild to moderate IPF [38]. The situation is, however, different when evaluating patients with severe disease. In a meta-analysis of placebo data of clinical trials of IPF, annual mortality in studies selecting mild-moderate patients was 8%, but in trials including moderate-severe patients it was 19% [39], in keeping with the data from TIPAC [14] and the epidemiology of the disease [2]. The event rate of mortality and hospitalisations is even higher when selecting patients with severe disease (up to 16% in 3 months [40]). Our primary outcome also meets the European Medicine Agency criteria for composite endpoints, as hospitalisation is an important predictor of mortality [25]. It can be easily and reliably assessed without patient involvement and is the least likely criterion to be influenced by withdrawal from the trial or unintentional or unavoidable unblinding of patients.

We have chosen to evaluate health-related quality of life by a number of different tools. All of the questionnaires are short and easy to complete, as we are cognisant of research participant burden. We decided against using the St. George’s Respiratory Questionnaire: although this has been used in a number of clinical trials [41], it takes nearly 10 min, and participants find difficulty completing it unaided [7].

Co-trimoxazole may be exerting its effect by either antibiotic or non-antibiotic mechanisms. Infection is common in patients with IPF – even amongst those not receiving immunosuppression. In a meta-analysis of patients allocated to placebo from clinical trials of patients with IPF, reported rates of pneumonia were 37.1 per 1000 patient years in studies not permitting immunosuppression [39] which is even higher than in chronic obstructive pulmonary disease [42]. More than one third of patients with IPF are colonised with pathogenic bacteria [43] or *Pneumocystis jirovecii* [44], most of which are susceptible to co-trimoxazole. Two independent groups of researchers using 16S technology have shown that a heavy bacterial load [15] and a lung microbiota profile enriched with *Streptococcus* and *Staphylococcus* spp. [45] predict poor outcomes in IPF. We have chosen to monitor an antibiotic effect by capturing routine microbiological data for all patients.

Alternatively or additionally, co-trimoxazole may also have non-antimicrobial effects, particularly on neutrophil function. Sulphamethoxazole-related sulphonamides have effects on neutrophil chemotaxis [46] and superoxide production [47]. Co-trimoxazole or its individual components (trimethoprim and sulfamethoxazole) also inhibit neutrophil post-phagocytic, myeloperoxidase-mediated protein iodination [48] and neutrophil respiratory burst [49, 50]. Oxidant stress has been implicated in alveolar epithelial injury [51], and epithelial-mesenchymal transition [52] in IPF, and IPF patients have increased concentrations of 8-isoprostane in exhaled breath condensate [53]. Moreover, neutrophils have an important role in causing oxidant stress in IPF [54], and neutrophilic alveolitis features frequently [55]. Furthermore, higher neutrophil counts in sputum are associated with worse lung function [56] and the percentage of bronchoalveolar lavage fluid (BALF) neutrophils at diagnosis is an independent predictor of mortality [57]. We will be assessing disease-modifying effects of co-trimoxazole by assessing recognised prognostic biomarkers in the serum in all patients who will also undergo measurement of neutrophil elastase at the end of the trial.

It is inevitable that many participants enrolled in this trial will be frail in view of their age and disease severity. For this reason we decided to keep the research burden to a minimum. The project has been designed so that the trial visits align with routine follow-up assessments for IPF patients, and the visit time points are sufficiently flexible to permit this. In addition (1) we have, for two of the visits, permitted safety blood tests to be undertaken in primary care and (2) have allowed adverse event assessments to be undertaken by phone.

This trial will determine whether co-trimoxazole is efficacious in terms of reducing mortality and or hospitalisation and should also provide some insight into its mechanism of action. Should it be found to have beneficial effects due to its antibiotic activity, further studies may be undertaken using narrower-spectrum antibiotics. Alternatively, if its activity is due to non-antibiotic mechanisms, such as effects on neutrophil activity in IPF, further lines of research may be possible using drugs targeting these mechanisms but lacking antimicrobial activity, thereby obviating the collateral risks of disrupting gut flora and selecting resistance.

